#### OS

The duration of OS will be calculated as the time between pathologic confirmation of local recurrence of NPC and the date of death from any cause. Patients who do not die or who are not lost to follow-up will be censored at the date of the last follow-up.

#### Progression-free survival

Progression-free survival will be defined as the time between the initiation of neoadjuvant chemotherapy or the start of CIRT and the date of disease recurrence or progression at any body part. Patients who do not die or who are not lost to follow-up and present no evidence of disease progression will be censored at the date of the last follow-up.

### Assessment of toxicity, safety, and other parameters

#### Toxicity and safety parameters

CTCAE v. 4.03 will be used for the monitoring and reporting of all toxicity and adverse events observed during and after the completion of study treatments [25]. Patients will be evaluated weekly by complete history, physical examination, and lab tests to determine the safety and toxicity of induction chemotherapy (if applicable) and CIRT plus concurrent chemotherapy. These evaluations will be conducted at each on-treatment appointment and at each follow-up clinical visit.

#### Other parameters

Peripheral blood will be collected to measure circulating Epstein-Barr virus (EBV) DNA and/or other tumor markers. These parameters may be used to predict the extent of disease or treatment outcome, or for future research purposes that may or may not be directly related to the current trial. A separate informed consent for this specimen collection will be required from the patients.

### Follow-up after trial completion

#### Follow-up

After completion of the study treatment, all patients will be required to be followed up regularly, indefinitely or until death, according to our institutional follow-up protocol for head and neck cancers. The first and second follow-up will be scheduled at 1 and 3 months after the completion of radiotherapy, respectively. Unless otherwise clinically necessary, follow-up sessions will then be scheduled every 3 months in the first 3 years, every 6 months in the following 2 years, and annually thereafter. Each follow-up examination will include a complete history and physical examination, MRI or CT scans with contrast of those for the head and neck area, and blood tests (including complete blood counts, serum electrolyte levels, pituitary function, and liver/renal function), and EBV DNA copies. Whole-body PET/CT scans is optional but preferable over thoracic and/or abdominal CT scans, and bone scans if clinically indicated.

#### Treatment at tumor progression

After completion of CIRT plus concurrent chemotherapy, further treatment, including salvage chemotherapy, surgical resection, a third course of radiation for locoregional recurrence, systemic treatment with chemotherapy, or targeted therapy may be clinically necessary in case of disease recurrence or progression. These treatment decisions will be made at the discretion of the treating physician and/or team.

### Statistics (see footnote 1)

#### Phase I trial

The primary objective is to determine the CIRT dose when used with concurrent cisplatin-based chemotherapy, which is associated with a DLT in less than 25% of previously treated NPC patients with a local recurrence. DLT is defined as any grade 4 toxicity (CTCAE v. 4.03) that is possibly, probably, or definitely associated with CIRT that occurred within 6 months after completion of re-irradiation [24]. Treatment-induced adverse effects also include deterioration in Eastern Cooperative Oncology Group performance status to ≥3 that develops during the same follow-up period. The secondary objectives are OS and local progression-free survival. The MTD of CIRT for re-irradiation used with concurrent cisplatin-based chemotherapy will be determined at the end of phase I trial.

Dose levels of CIRT will be assigned based on the TITE-CRM algorithm [21]. During the trial, pDLT will be continually updated, using data from all enrolled patients and their updated outcomes obtained through follow-up visits. Patients with partial follow-up at a time of new enrollment (i.e., <4 months) will be weighted by the proportion of the follow-up time completed. Newly enrolled patients will be assigned to the dose that is estimated to have a pDLT closest to but not higher than 0.25.

Four patients will be entered to the starting dose level. Dose escalation is restricted to one level between any 2 patients. Prior to escalation, at least 1 patient must have completed the full course of treatment and the full observation period (6 months) at the previous dose level without a DLT. Six dose levels and their initial estimation of the pDLT are planned within the phase I trial (Table 1). The dose will be increased until DLT is observed or when 65 GyE is reached.

As described above, the phase I trial was designed to accrue up to 25 patients. We estimate that 4 patients will be accrued each month. Patients who complete 90% or more of the planned CIRT dose will be considered evaluable. Patients who complete 90% or more of the planned CIRT dose but become un-evaluable for 6 months will be counted as evaluable in the final analysis and weighted by the proportion of the observation period for which they were evaluable. Replacement of any accrued patient can only be considered if the patient did not complete therapy for reasons other than toxicity.

At the end of the trial, a simple two-parameter logistic regression model will be used to estimate the pDLT at each dose level. Secondary endpoints are the response of tumor to CIRT, local progression-free survival, OS, and other toxicity and safety data on the studied dose levels. The Kaplan–Meier method will be used to evaluate the OS and local progression-free survival of all patients. SAS v.9.1 software (SAS Institute Inc, Cary, NC, USA) will be used for statistical analyses. The Cox proportional hazards model will be used for multivariate analysis, as the univariate results indicate.

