### Objectives

#### Phase I trial

The primary objective is to determine the MTD of CIRT combined with concurrent chemotherapy in the treatment of locally recurrent NPC, by observing the acute or subacute grade 4 or 5 toxicities [Common Terminology Criteria for Adverse Events (CTCAE) v. 4.03] that are possibly, probably, or definitively caused by the treatments [25]. The secondary objective is to evaluate the local progression-free survival and OS after re-irradiation using the combined treatment.

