### Trial design and schedule

#### Phase I trial: dose escalation to determine MTD

The purpose of the phase I trial is to determine the MTD of salvage raster-scanning CIRT with concurrent cisplatin-based chemotherapy for locally recurrent NPC. Patients who meet the inclusion criteria will be treated with chemotherapy and this dose-escalating CIRT scheme, and acute and subacute toxicity during the treatments and within 4 months after CIRT will be observed.

The study includes 6 increasing dose regimens starting at 52.5 GyE (2.5 GyE × 19 fractions) up to 65 GyE (2.5 GyE × 26 fractions) using the TITE-CRM design of phase I trials, with the starting dose/fraction at 55 GyE delivered daily in 22 fractions. The trial will be concluded at 65 GyE if the MTD is not reached, and 65 GyE/26 fractions will be the recommended dose/fractions for the phase II trial. The probability of dose limiting toxicity (pDLT) for each dose level is estimated based on published data for re-irradiation with CIRT to the head and neck area (Table 1).

**Table 1 Tab1:** Treatment schedule (CIRT plus concurrent chemotherapy) for dose escalation in patients with locally recurrent nasopharyngeal carcinoma (NPC)

Dose level	Dose and fractionation	Total dose (GyE)	pDLT (%)	BED2 (GyE)	BED9 (GyE)
1	2.5 GyE × 21 fractions	52.5	<5	118.1	67.1
*2*	*2.5 GyE* *×* *22 fractions (starting dose)*	*55*	*10*	*123.8*	*70.3*
3	2.5 GyE × 23 fractions	57.5	20	129.4	73.5
4	2.5 GyE × 24 fractions	60	30	135.0	76.7
5	2.5 GyE × 25 fractions	62.5	40	140.6	79.9
6	2.5 GyE × 26 fractions	65	50	146.3	83.1

The starting dose of the trial is at 2.5 GyE *×* 22 (in italics)

*CIRT* carbon-ion radiotherapy, *GyE* gray equivalent, *pDLT* probability of dose-limiting toxicities, *BED* biological effective dose, *BED2* cumulative BED with an α/β ratio of 2, *BED9* cumulative BED with an α/β ratio of 9

A maximum of 25 patients for the 6 dose levels (starting at 55 GyE) is projected for phase I trial (i.e., the dose-escalating stage of the trial). Based on our clinical load, we expect to recruit an average of 1 patient per week. We expect that the phase I trial will be completed in 24 months, since the first patient at each dose level will be followed up for 4 months before dose escalation.

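### The phase I DLT definition that drives dose assignment stops at grade 4, so read literally it leaves out treatment-related death and contradicts the primary objective

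*Protocol article*

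**What the plan says.** The protocol article defines the toxicity that determines the MTD in two places.

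- **Objectives, Phase I trial.** The MTD is to be found "by observing the acute or subacute grade 4 or 5 toxicities" "that are possibly, probably, or definitively caused by the treatments". The treatments here are CIRT with concurrent chemotherapy.
- **Statistics, Phase I trial.** "DLT is defined as any grade 4 toxicity (CTCAE v. 4.03) that is possibly, probably, or definitely associated with CIRT", within 6 months after re-irradiation ends. The next sentence adds deterioration to ECOG performance status 3 or worse, but as a treatment-induced adverse effect and not expressly as a DLT.

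The Statistics definition is the operative one. It feeds the continual update of pDLT and the assignment rule: "Newly enrolled patients will be assigned to the dose that is estimated to have a pDLT closest to but not higher than 0.25". It also feeds the escalation precondition, under which at least one patient must have completed "the full observation period (6 months) at the previous dose level without a DLT".

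The observation period is also given in two lengths. The DLT definition and the escalation precondition use 6 months. The trial design section says "acute and subacute toxicity during the treatments and within 4 months after CIRT will be observed", and the TITE-CRM weighting says "Patients with partial follow-up at a time of new enrollment (i.e., <4 months) will be weighted" by the fraction of follow-up completed.

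**The concern.** The two definitions differ in grade (4 against 4 or 5) and in attribution (CIRT against the treatments). Nothing elsewhere in the article says grade 4 or higher, or states that a treatment-related death is a DLT. Elsewhere the authors name grade 5 when they mean to include it: grade 4 or 5 in the objective, and grades 3–5 when reviewing earlier series. The ECOG sentence does not close the gap, because it widens a different term and describes deterioration, which does not clearly cover a sudden death.

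Fatal toxicity is a real possibility in this setting. The background section on re-treatment challenges says high-dose re-irradiation can kill through necrosis, infection or carotid hemorrhage. The dose-selection section reports that almost 70% of mucosal necrosis after IMXT re-irradiation arose within 6 months, which is inside the DLT window. A death that is left out of the count can only pull the estimated pDLT down and push the MTD up, and the phase II section adopts that MTD as the recommended dose.

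**Working it through.** The plan gives no figure for this point that could be reproduced. The check is a comparison of the text, followed by a one-event illustration.

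**1. The definitions side by side**

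| | Objectives | Trial design | Statistics: DLT and escalation | Statistics: weighting |
|---|---|---|---|---|
| Grade | 4 or 5 | not stated | 4 | – |
| Attribution | the treatments | not stated | CIRT | – |
| Window after CIRT | acute or subacute | 4 months | 6 months | 4 months |

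**2. One-event illustration**

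Inputs from the article:
- four patients at the starting dose, 55 GyE (level 2);
- initial pDLT values from Table 1: 0.10, 0.20, 0.30, 0.40, 0.50 for levels 2 to 6, with 0.05 taken for the level 1 entry of below 5%;
- a cap of 0.25 and at most one level up at a time.

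Assumptions, because the article does not give them: the working model and its prior. Two common one-parameter models were used, with prior b ~ N(0, v):
- power: p_j = s_j^exp(b), where s_j is the Table 1 value;
- logistic with intercept 3: logit p_j = 3 + exp(b)·x_j, with x_j = logit(s_j) − 3.

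Scenario: all four patients are fully followed, one dies of treatment-related toxicity with no earlier countable grade 4 event, and three are DLT-free at 6 months. The escalation precondition needs only one DLT-free patient, so it is met. The Statistics definition read literally gives y = 0 of 4, and the Objectives definition gives y = 1 of 4. The likelihood is p_2^y (1 − p_2)^(4 − y).

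Posterior mean pDLT at 57.5 GyE (level 3):

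| Model | y | v = 0.25 | 0.5 | 1.0 | 1.34 | 2.0 |
|---|---|---|---|---|---|---|
| Power | 0 | 0.162 | 0.141 | 0.117 | 0.107 | 0.093 |
| Power | 1 | 0.285 | 0.321 | 0.355 | 0.367 | 0.382 |
| Logistic | 0 | 0.115 | 0.091 | 0.069 | 0.061 | 0.051 |
| Logistic | 1 | 0.357 | 0.382 | 0.400 | 0.405 | 0.411 |

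All ten y = 0 values are below 0.25, so the next patient goes up to 57.5 GyE. All ten y = 1 values are above 0.25, so the next patient stays at 55 GyE or drops to 52.5 GyE.

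**3. Where the reversal fails**

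- Tighter priors, 1 of 4: the power model gives 0.245 at v = 0.10 and 0.226 at v = 0.05, so escalation is allowed under either definition. The logistic model gives 0.314 and 0.280 and still reverses.
- More patients at 55 GyE, power model: one death in 8 gives 0.231 (v = 0.25), 0.240 (v = 0.5) and 0.251 (v = 1.34). One in 10 gives 0.21–0.22 at all three.

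**4. Window**

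A patient who is DLT-free 4 months after CIRT has weight 4/4 = 1.00 under the 4-month rule and 4/6 = 0.67 under the 6-month window.

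**The case against.** The strongest reply is that this is a drafting slip. The primary objective names grade 5, no passage excludes deaths, and the investigators would have to act against their own objective to call a toxic death DLT-free. The IRB, acting as the safety board, reviews the trial semi-annually. The ECOG sentence directly follows the DLT definition and refers to the same follow-up period, so it can be read as extending that definition. On that reading a patient who declines to ECOG 3 or worse before dying is already counted.

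The evidence on size is also indirect. The necrosis figure concerns IMXT and is not a death rate. The article reports low short-term toxicity after CIRT alone and gives no rate of grade 5 events within 6 months of CIRT. The illustration depends on an early death and on the chosen priors.

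Most of this is fair. The intent was very likely grade 4 or higher, the ECOG sentence may narrow the gap, and the reversal is conditional, as shown above. It does not remove the problem. A sudden carotid hemorrhage need not be preceded by a recorded grade 4 event or a performance-status decline, and an escalation rule should not rest on a reader's guess. The Statistics section also says that the dose rises until a DLT is seen. If that sentence is applied, a single counted event stops escalation whatever the model estimates, so whether a death counts matters more, not less.

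The attribution difference is minor in itself: since only CIRT is escalated, either wording is defensible, but the two sections must agree. The window conflict is a separate inconsistency that adds nothing to the grade 5 point. It belongs here only because the same sentence has to be corrected.

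**Conclusion.** The concern holds. The operative DLT definition contradicts the phase I primary objective and, applied literally, can score a treatment-related death as no DLT. The direction of the bias is certain: pDLT too low and MTD too high. The overall size cannot be derived, because it depends on how many grade 5 events occur without an earlier countable grade 4 event, and the document gives no such share. The one-death scenario shows only that the two definitions can lead to opposite dose decisions from the same data. It rests on the assumed models and priors and on the death falling among the first four patients. This should be fixed: the likely intent is clear, but the safety rule is wrong as written.

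**What to change.** In the Statistics section, define a DLT as any grade 4 or 5 toxicity (CTCAE v. 4.03) at least possibly related to study treatment, from the first day of CIRT and cisplatin to 6 months after CIRT. Use the same 6-month window in the trial design section and in the TITE-CRM weighting. Make the attribution identical in Objectives and Statistics. Attribution to the treatments follows the stated primary objective; limiting it to CIRT is acceptable if Objectives is changed to match. State whether ECOG deterioration to 3 or worse is itself a DLT.

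One minor clarification: the plan says "Patients who complete 90% or more of the planned CIRT dose will be considered evaluable". Add that a patient with a DLT is evaluable at full weight whatever CIRT dose was delivered.

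The cost is a few words in three sections. Estimated DLT rates may be slightly higher and the MTD slightly lower, more so if purely cisplatin-related events are counted. Against the trial design section's timetable, the 6-month window adds up to 2 months per escalation, at most 4 × 2 = 8 months over the four steps from 55 to 65 GyE. The Statistics section already requires those 6 months before escalation.

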#### Concurrent chemotherapy

The administration of concurrent cisplatin-based chemotherapy will start on the first day of CIRT and will consist of weekly cisplatin (40 mg/m^2^) during CIRT for a maximum of 5 cycles. Chemotherapy at the full dose will be delivered, and no adjustment will be allowed unless grade 4 chemotherapy-induced toxicities occur. The start of chemotherapy can be postponed if a patient’s neutrophil count drops below 2000/µL or the platelet count drops below 100,000/µL. Chemotherapy can be suspended if a patient’s creatinine clearance rate is less than 50 mL/min.

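### The formal DLT definition leaves out the treatment weeks, while the design and objectives sections include toxicity on treatment, so one event can be classified two ways and the selected dose could be too high

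*Protocol article*

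**What the plan says.** All references are to the Protocol article.

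- **Statistics, Phase I trial** holds the only formal definition. A DLT is a grade 4 toxicity "that is possibly, probably, or definitely associated with CIRT that occurred within 6 months after completion of re-irradiation". The next sentence adds a decline in performance status and ties it to that same follow-up period.
- **Same section, escalation condition:** before the dose goes up, "at least 1 patient must have completed the full course of treatment and the full observation period (6 months) at the previous dose level", and that patient must be free of DLT.
- **Same section, weighting:** "Patients with partial follow-up at a time of new enrollment (i.e., <4 months) will be weighted by the proportion of the follow-up time completed".
- **Phase I trial: dose escalation to determine MTD:** "acute and subacute toxicity during the treatments and within 4 months after CIRT will be observed".
- **Objectives, Phase I trial:** the maximal tolerated dose (MTD) is found "by observing the acute or subacute grade 4 or 5 toxicities" "that are possibly, probably, or definitively caused by the treatments". The abstract likewise names acute and subacute toxicities as the primary endpoints of phase I.
- **Concurrent chemotherapy** foresees severe events during the course: "no adjustment will be allowed unless grade 4 chemotherapy-induced toxicities occur".
- **Toxicity and safety parameters** requires weekly assessment during CIRT plus chemotherapy.

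**The concern.** DLT status drives three decisions in phase I: the running update of the DLT probability (pDLT), the DLT-free condition for opening the next level, and the end of escalation. The recommended phase II dose follows from these. The definition that feeds them places the event after completion of re-irradiation. The sections that state the purpose of phase I include toxicity during treatment.

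If the definition is applied as printed, CIRT-related grade 4 events in the treatment weeks drop out of the count. The pDLT estimates would then be too low, and the method could settle on a level whose real DLT rate exceeds the 25% limit.

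**Working it through.** **Step 1. Classify the same records under each text.** CIRT takes 21 to 26 fractions at 5 per week, so 21/5 = 4.2 to 26/5 = 5.2 weeks. The records are hypothetical.

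| Record | Statistics section, literal | Statistics section, as end limit only | Objectives and design section |
|---|---|---|---|
| Grade 4, CIRT-related, week 4 of CIRT, resolved | Not a DLT | DLT | In scope |
| Grade 4, CIRT-related, month 3 after CIRT | DLT | DLT | In scope |
| Grade 4, CIRT-related, month 5 after CIRT | DLT | DLT | Outside the 4 months |
| Grade 5, CIRT-related, month 2 after CIRT | Grade 5 not named | Grade 5 not named | In scope |
| Grade 4, cisplatin alone, on treatment | Not a DLT | Not a DLT | In scope (caused by the treatments) |

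Row 1 is the point at issue. On the literal reading that patient, once followed for 6 months, could be the one whose record permits escalation. Rows 3 to 5 show that length, grade and attribution conflict as well.

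**Step 2. Effect on the selected level.** The document gives no phase I operating characteristics to reproduce, so this is a sensitivity calculation.

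- Inputs: Table 1 pDLT of under 5, 10, 20, 30, 40 and 50% for levels 1 to 6, taken as the truth. The rule is pDLT closest to but not above 0.25.
- Assumption: a share s of all DLTs occurs on treatment and goes uncounted. The document does not give s; 0 to 50% is shown.
- Formula: counted pDLT = true pDLT × (1 − s). A level with true rate p passes once s ≥ 1 − 0.25/p.

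| s | Level 3 (true 20%) | Level 4 (true 30%) | Level 5 (true 40%) | Level 6 (true 50%) | Highest level passing |
|---|---|---|---|---|---|
| 0 | 20% | 30% | 40% | 50% | 3 |
| 10% | 18% | 27% | 36% | 45% | 3 |
| 20% | 16% | 24% | 32% | 40% | 4 |
| 30% | 14% | 21% | 28% | 35% | 4 |
| 50% | 10% | 15% | 20% | 25% | 6 |

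Thresholds: level 4 at 1 − 0.25/0.30 = 16.7%; level 5 at 1 − 0.25/0.40 = 37.5%; level 6 at 1 − 0.25/0.50 = 50%.

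**Step 3. Simulation, for direction only.** A simplified CRM was used: one-parameter power model, Table 1 as both skeleton and truth with 0.04 for level 1, complete follow-up, 25 patients, the first 4 at level 2, no skipping of levels, 2,000 runs. The chance of selecting a level with true pDLT above 25% was 26% at s = 0, 35% at 10%, 49% at 20%, 60% at 30% and 80% at 50%. The mean true pDLT at the selected level was 20, 22, 25, 28 and 35%. Time-to-event versions at 1 patient per month gave about 30% at s = 0, 54 to 57% at s = 30% and 76 to 77% at s = 50%.

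**Step 4. Dependence on accrual.** One patient per month fits the expected 24 months for phase I (25/24 ≈ 1 per month). The Statistics section states 4 per month. At that pace without pauses, 25 patients enter in 25/4 = 6.25 months, before anyone completes about a month of CIRT plus 6 months. No escalation occurs, and the chance of recommending a tried level above 25% is 0% whatever s is. If untried levels may be recommended, the chance rises from 29% at s = 0 to 51% at s = 30%.

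**The case against.** A reader might infer that the trial counts only events after completion and that its MTD is therefore biased upward. The document does not support that as fact.

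- The definition does not say that only later events count, and it gives no start date. It can be read as setting the last day on which a DLT may occur.
- The abstract, the objectives, the design section and the weekly on-treatment assessment all fit that reading. Being free of DLT, in the escalation condition, can naturally cover both the course and the 6 months after it.
- Cisplatin toxicity in the treatment weeks is only partly relevant. The definition requires association with CIRT, so an event due to cisplatin alone stays outside whatever the start of the window.
- A large s has no support in the document. The Discussion reports that all CIRT-alone patients completed 57.5 GyE without moderate or severe adverse effects, and the Background stresses late injury. Neither settles s once cisplatin is added. Nor does the document say which period the Table 1 values cover.

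These points rule out a claim of demonstrated bias. They do not remove the inconsistency. The literal reading has support in the same section: the reference to the same follow-up period, the listing of the treatment course and the observation period as separate items, and the updating of pDLT from follow-up visits, which the Follow-up section schedules from 1 month after radiotherapy. This is also not detail left to a fuller document, because the article prints a definition and that definition conflicts with its own objective.

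**Conclusion.** The concern holds as an inconsistency in the primary phase I endpoint. The printed definition omits the treatment period, and the objectives and design section include it. Two assessors could classify the same on-treatment grade 4 event differently, and the next patient's dose could depend on which reading was used.

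If the literal reading is applied, any error in pDLT is downward and the selected dose could be too high. The size is not known. With Table 1 as the truth, nothing changes at s = 10%, and the 30% level passes the 25% rule from s of about 17%. The simulated probabilities rest further on the model and on accrual of about 1 patient per month or complete follow-up, so they show direction and not a forecast for this trial.

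**What to change.** Reconcile the abstract, Objectives, the dose-escalation section and Statistics into one DLT definition that states explicitly when the window starts and whether on-treatment events count. The objectives and design section indicate that they should. Then:

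1. Use that same window in the definition, in the DLT-free escalation condition and in the TITE-CRM weights.
2. Settle in the same edit the window length (4 or 6 months), the grade (4, or 4 and 5) and the attribution (CIRT, or the treatments).
3. State how a patient is classified who stops before 90% of the planned CIRT dose because of toxicity. As written, that patient does not meet the evaluability criterion, replacement is not allowed, and the text does not say whether a DLT is counted.
4. Reclassify patients already enrolled under the agreed definition.

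The cost is a short amendment. No new data are needed, since toxicity is already assessed weekly on treatment. The downside is that the estimated pDLTs may become less favourable.

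### Phase I uses a 6-month DLT window, but the TITE-CRM cut-off for partial follow-up and one of its two escalation waits are 4 months

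*Protocol article*

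**What the plan says.** The protocol article describes the phase I rules in two places.

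Statistics, Phase I trial:
- DLT definition: a grade 4 toxicity at least possibly associated with CIRT "that occurred within 6 months after completion of re-irradiation".
- Escalation condition: at least one patient must have completed treatment and "the full observation period (6 months) at the previous dose level without a DLT".
- Final analysis: patients who received at least 90% of the planned dose but "become un-evaluable for 6 months will be counted as evaluable in the final analysis", weighted by the share of the observation period for which they could be evaluated.
- Interim dose assignment: "Patients with partial follow-up at a time of new enrollment (i.e., <4 months) will be weighted by the proportion of the follow-up time completed". The next patient gets the dose whose estimated pDLT is nearest to 0.25 without exceeding it.

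Trial design and schedule, Phase I trial:
- Observation: "acute and subacute toxicity during the treatments and within 4 months after CIRT will be observed".
- Escalation: the first patient at each level is followed for 4 months before the dose goes up. This wait is the reason given for expecting phase I to take 24 months.

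The Statistics section therefore uses 6 months three times and 4 months once. The design section uses 4 months twice.

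**The concern.** A TITE-CRM needs one observation window. The DLT definition, the time at which a DLT-free patient counts in full, and any minimum wait before escalation should all refer to it. Here they do not, and two things follow.

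- **Weights.** A patient who is DLT-free at month 4 no longer falls under the partial-follow-up rule and so counts as a completed non-event. By the protocol's own definition that patient can still have a DLT in months 5 and 6. Complete credit for incomplete follow-up lowers the interim pDLT and so favours escalation.
- **Escalation gate.** The two sections give different conditions for opening the next level. Under the design section it can open two months before the DLT window of the current level's first patient has closed. Under the Statistics section it cannot.

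This is re-irradiation with concurrent chemotherapy, and the Background describes mucosal necrosis as potentially life-threatening. Site staff should not have to choose between two escalation rules.

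**Working it through.** **1. Do the windows share a time origin?** The design section counts its 4-month observation period after CIRT. The DLT definition counts 6 months from completion of re-irradiation. These are the same point, so a different clock does not explain the gap. The endpoint is also the same: the Objectives section determines the MTD from acute or subacute toxicity, and that is what the design section observes for 4 months.

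**2. Weight of a DLT-free patient.** Weight = min(1, follow-up / window).

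| Months after CIRT | 4-month window | 6-month window |
|---|---|---|
| 3 | 3/4 = 0.75 | 3/6 = 0.50 |
| 4 | 1.00 | 4/6 = 0.67 |
| 5 | 1.00 | 5/6 = 0.83 |
| 6 | 1.00 | 1.00 |

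The protocol states no denominator. If 6 months were the denominator but only patients under 4 months counted as partial, the weight would still be 1.00 from month 4.

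**3. The 24-month estimate.** Inputs: start at level 2; 22, 23, 24, 25 and 26 fractions at levels 2 to 6 (Table 1); five fractions per week; 12/52.18 = 0.230 months per week. Counting only the first patient at each level, and entering that patient as soon as the level opens:

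Time per level = (fractions / 5) × 0.230 + window. For level 2 this is 4.4 × 0.230 + 4 = 5.0 months, or 4.4 × 0.230 + 6 = 7.0 months.

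| Window of first patient complete through | 4-month gate | 6-month gate |
|---|---|---|
| Level 2 | 5.0 | 7.0 |
| Level 3 | 10.1 | 14.1 |
| Level 4 | 15.2 | 21.2 |
| Level 5 | 20.3 | 28.3 |
| Level 6 | 25.5 | 35.5 |

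The protocol gives no formula for its 24 months, so the figure cannot be reproduced exactly. It lies between the 4-month values for levels 5 and 6 (20.3 and 25.5), which agrees with the reason the protocol gives for it.

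**4. How much the weights matter (illustration only).** The article does not give the interim working model, the prior or the DLT timing. Assumed: pDLT = skeleton^exp(b); skeleton from Table 1, with the entry below 5% taken as 5%; b normal with mean 0 and variance 1.34.

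- *Interim estimate.* Take four complete DLT-free patients at level 2. At level 3 take one DLT, one complete DLT-free patient and two to five DLT-free patients at month 4. Use prior variance 1.34 or 0.5, and plug-in or posterior-mean estimates, which gives 16 variants. The 4-month weights lower the level-4 pDLT by 0.017 to 0.036 in all 16 and move it across 0.25 in 8.
- *Whole trial.* Truth equal to the skeleton, DLT onset uniform over 6 months, 25 patients over 24 months, 6-month gate kept, 2,000 runs. Patients treated at level 4 or above: 3.3 with 4-month weights against 2.9 with 6-month weights. Runs with the final MTD at level 4 or above: 28.6% against 27.4%. If escalation also stops at the first DLT: 1.4 against 1.3 patients, and 12.1% against 12.0%.

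**The case against.** The best reply is that this is a slip of wording with little effect. The Statistics gate is the stricter one, and a team that follows it also satisfies the 4-month wait. The weighting bias depends on how a short parenthesis is read, and the section's other weighting rule uses 6 months. Every one of the 16 interim variants contains a DLT, and the protocol also says "The dose will be increased until DLT is observed or when 65 GyE is reached", which read literally would block escalation in all of them. On the illustrative figures the final MTD hardly moves.

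Most of this stands. It limits the size of the effect but does not remove the contradiction. Nothing in the article says that the stricter gate prevails, and the 4-month value stands in the rule that assigns doses.

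A reader might go further and infer two things that the documents do not support.

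- *That 24 months is impossible under a 6-month gate.* It is not: the first patient at level 4 completes the window at month 21.2. Table 1 puts level 3 at 20% and level 4 at 30% against the 0.25 limit, so the protocol's own expectation is an MTD near level 3. The full climb to level 6 exceeds 24 months even with a 4-month gate (25.5).
- *That the accrual estimate ("We estimate that 4 patients will be accrued each month") shows the 6-month gate to be unworkable.* At that rate without a pause, patient 25 enrols at month 24 × 0.25 = 6.0. A 4-month gate fails almost as badly: level 3 opens at month 5.0, at most four patients could enter it, and level 4 is never reached. The problem therefore does not come from the difference between 4 and 6 months. The design section expects 24 months for 25 patients at about one per week, so waiting is already implied. Accrual is a separate matter.

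**Conclusion.** The point holds as an internal contradiction that should be fixed. One design parameter has two values, both counted from the end of CIRT, and no text reconciles them.

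What follows from the document alone: the two sections give different conditions for opening the next level, two months apart, and on the natural reading a DLT-free patient is over-weighted between months 4 and 6 (1.00 instead of 0.67 at month 4 and 0.83 at month 5). The direction is toward a lower interim pDLT.

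What rests on assumptions: the size of that bias. With the 6-month gate kept and the model assumed above, the weights add at most a fraction of a patient at the higher levels and change the share of runs with a high final MTD by about 1 percentage point or less. The documents do not support a claim that the MTD would be materially wrong. No sample size or power figure depends on this point.

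**What to change.** Use 6 months after completion of CIRT in both sections:

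- toxicity observation period: during treatment and for 6 months after CIRT;
- interim TITE-CRM weight for a DLT-free patient: months of follow-up after CIRT divided by 6, capped at 1;
- escalation: at least one patient at the current level with the full 6 months and no DLT, stated identically in both places.

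Six months is the better choice because it is already the DLT definition. Follow-up at 1 and 3 months and then every 3 months already includes a month-6 visit. The Background also reports, from photon re-irradiation, that almost 70% of mucosal necrosis arose within 6 months.

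Restate the 24-month estimate, because its stated reason is the 4-month wait. With a 6-month gate the first-patient minimum is about 21 months through level 4, 28 through level 5 and 35–36 through level 6.

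The cost is a change of wording, with no added visit or patient. Phase I may last longer if escalation goes beyond level 4, but that already follows from the gate in the Statistics section.
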